## **5. TREATMENT OF SUBJECTS**

### **5.1 Investigational product/treatment**

The intervention consists of the implementation of the S-team, which is a quality improvement dictated by the national guideline LSKA. The S-team will consist of a specialized thrombosis nurse as case manager, hematologist, medical leader Thrombosis Service, hospital pharmacist/clinical pharmacologist, cardiologist and a pediatric hematologist. An anesthesiologist, neurologist, pulmonologist, dermatologist, clinical chemist, emergency physician and (orthopedic) surgeon may be added to the team when necessary.

The main tasks of the S-team are:

- Drafting of local guidelines
- Monitoring of the medication by the hospital pharmacist/clinical pharmacologist focused on patients that are treated with antithrombotics
- Patient instructions
- Proper handover to either the Thrombosis Service or the general practitioner, and to the community pharmacist, at the moment of hospital discharge
- Educating physicians, nurses and hospital pharmacists
- Offering consultation for professionals in- and outside the hospital

### **5.2 Use of co-intervention**

None.

### **5.3 Escape medication**

N.a.

## **6. INVESTIGATIONAL PRODUCT**

### **6.1 Name and description of investigational product(s)**

N.a.

### **6.2 Summary of findings from non-clinical studies**

N.a.

### **6.3 Summary of findings from clinical studies**

N.a.

### **6.4 Summary of known and potential risks and benefits**

N.a.

### **6.5 Description and justification of route of administration and dosage**

N.a.

### **6.6 Dosages, dosage modifications and method of administration**

N.a.

### **6.7 Preparation and labelling of Investigational Medicinal Product**

N.a.

### **6.8 Drug accountability**

N.a.

## **7. NON-INVESTIGATIONAL PRODUCT**

### **7.1 Name and description of non-investigational product(s)**

N.a.

### **7.2 Summary of findings from non-clinical studies**

N.a.

### **7.3 Summary of findings from clinical studies**

N.a.

### **7.4 Summary of known and potential risks and benefits**

N.a.

### **7.5 Description and justification of route of administration and dosage**

N.a.

### **7.6 Dosages, dosage modifications and method of administration**

N.a.

### **7.7 Preparation and labelling of Non Investigational Medicinal Product**

N.a.

### **7.8 Drug accountability**

N.a.

## 8. METHODS

### 8.1 Study parameters/endpoints

#### 8.1.1 Main study parameter/endpoint

Composite endpoint: proportion of patients with  $\geq 1$  bleeding (major bleeding and mild to moderate clinically relevant non-major bleeding) or  $\geq 1$  thrombotic events from time to start with antithrombotic medication (or hospitalization) until 3 months after hospitalization.

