### 4.2 Inclusion criteria

In order to be eligible to participate in this study, a subject must meet all of the following criteria:

- Patients that are or will be treated with antithrombotics in the Erasmus MC or in the Reinier de Graaf hospital.
- Informed consent (we will ask permission from the patients to collect community pharmacy and to fill out four questionnaires).
- Only the first hospital admission of a patient within the study period will be included (readmission is an endpoint).

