|                | Length*                                                                                                                                                                                                                                               |
|                | Community pharmacist**\$                                                                                                                                                                                                                              |
|                | Reason for hospitalization*                                                                                                                                                                                                                           |
|                | Reason for exclusion                                                                                                                                                                                                                                  |
|                | (Co)morbidity*                                                                                                                                                                                                                                        |
|                | Day of hospitalization*                                                                                                                                                                                                                               |
|                | Any surgery (coded with Verrichtingen code  ) or diagnosis during hospitalization*                                                                                                                                                       |
| Study outcomes | Bleeding (major bleeding and mild to moderate clinical relevant non-major bleeding) or thrombotic event during hospitalization*                                                                                                                       |
|                | Bleeding (major bleeding and mild to moderate clinical relevant non-major bleeding) or thrombotic event within 3 months after hospitalization^                                                                                                        |

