|                 | Overview of medication use three months after hospitalization (coded with ATC-code  )+                                                                                                                                                                                                                                                                                                                                                                                                                                                                                                                                        |

\*Obtained from medical record of the hospital information system

+Obtained from the community pharmacist and the Thrombosis Service

\$Obtained from the patient using questionnaire

^Obtained by sending a small questionnaire asking for visits to the general practitioner or hospital because of a bleeding or thrombotic event within 3 months after hospitalization.

***The primary outcome of the study is the proportion of patients with a composite endpoint consisting of  $\geq 1$  bleeding (major bleeding and mild to moderate clinical relevant non-major bleeding) or  $\geq 1$  thrombotic events during and 3 months after hospitalization.***

Patients treated with antithrombotics and/or antidotes in the Erasmus MC and in the Reinier de Graaf hospital will be included with the help of a clinical rule (table 1 and 2). The data from the medical record of the hospital information system is used to determine whether there is a bleeding (major bleeding and mild to moderate clinical relevant non-major bleeding) or thrombotic event in patients who are enrolled in the study.

After hospitalization data from community pharmacist, general practitioner and the Thrombosis Services are used. At discharge the patient will be asked to fill in a consent form. By signing the consent form, the patient gives permission to retrieve patient data from the community pharmacist, general practitioner and the Thrombosis Services.

Definition of terms:

The ISTH definitions of bleeding in patients are as follows:

- Major Bleeding in non-Surgical Patients
  - 1. Fatal bleeding, and/or
  - 2. Symptomatic bleeding in a critical area or organ, such as intracranial, intraspinal, intraocular, retroperitoneal, intra-articular or pericardial, or intramuscular with compartment syndrome, and/or

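### The primary endpoint window has two non-equivalent starting points, and no rule keeps out the bleed or thrombosis that caused the index admission

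*Protocol*

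**What the plan says.** The protocol states the primary endpoint window in two forms.

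- **Section 8.1.1** counts patients with at least one bleeding or thrombotic event "from time to start with antithrombotic medication (or hospitalization) until 3 months after hospitalization". The Summary and the first two secondary endpoints in 8.1.2 use the same window. The parenthesis offers a second starting point without saying to whom it applies.
- **Section 8.3.1** gives the primary outcome as bleeding or "thrombotic events during and 3 months after hospitalization". Medication start is not mentioned. Table 3 in that section has two event fields: a bleeding or "thrombotic event during hospitalization", and the same within 3 months afterwards.

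Four other statements decide who can enter with an event already present, and how it would be handled.

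- **Section 4.2** admits "Patients that are or will be treated with antithrombotics", so both current users and patients who start in hospital. Section 4.3 does not exclude patients admitted because of a bleed or thrombosis.
- **Section 8.3.1** has the clinical rule pick up "Patients treated with antithrombotics and/or antidotes". Antidote use can therefore flag a patient.
- **Section 8.3.1** on ascertainment: "The data from the medical record of the hospital information system is used to determine whether there is a bleeding" or thrombotic event. Onset after admission is not required.
- **Table 3** records "Reason for hospitalization" among the patient data, but no endpoint definition refers to it, and the table lists no onset date for endpoint events.

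**The concern.** The two statements are not equivalent. For a current user, medication start may lie long before admission; for a patient started in hospital, it lies after admission. The same patient can therefore be an endpoint case under one section and not under another.

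The sharpest consequence concerns the event that led to the index admission. Only the first admission in the study period is included, and the S-team works mainly through in-hospital medication monitoring, patient instruction and discharge handover (sections 5.1 and 8.3.3). It can generally not prevent an event that precedes that admission. To the extent that such events are counted, they add non-preventable cases to both phases and pull the comparison towards no effect. If their frequency differs between the two periods, for example through a shift in case mix, the uncontrolled before-after comparison is biased as well, in a direction that cannot be known in advance.

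**Working it through.** **1. Does the presenting event fall inside the window?**

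| Patient admitted with a bleed or thrombosis | Window starts at medication start (8.1.1) | Window starts at hospitalization (8.1.1 parenthesis, 8.3.1) |
|---|---|---|
| Already on antithrombotics | Inside: the event follows medication start | Not settled: the event is in the admission record and no new-onset rule removes it |
| Started on antithrombotics in hospital | Outside: the event precedes the first dose | Not settled, for the same reason |

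One cell is clearly inside, one clearly outside, and two depend on how the abstractor reads the text.

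**2. Reproducing the planned sample size**

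Inputs from section 4.4: composite rate p1 = 0.09 before and p2 = 0.055 after, alpha 0.05, power 0.80, 917 per phase. Sidedness is not stated; two-sided reproduces the figure.

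- Pooled two-proportion formula: m = [1.960·√(2·p̄(1−p̄)) + 0.842·√(p1(1−p1) + p2(1−p2))]² / d², with p̄ = 0.0725 and d = 0.035. This gives m = 860.5, so 861.
- Continuity correction: n = (m/4)·[1 + √(1 + 4/(m·d))]² = 916.8, so 917, as stated.

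**3. Power at 917 per phase**

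Power = Φ[(d − 1/n − 1.960·SE0)/SE1], where SE0 = √(2p̄(1−p̄)/n) and SE1 = √((p1(1−p1) + p2(1−p2))/n).

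For 9% against 5.5%: SE0 = 0.01211 and SE1 = 0.01208, so (0.035 − 0.00109 − 0.02374)/0.01208 = 0.842 and power is 80.0%. Without the continuity correction it is 82.4%.

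**4. Adding presenting events**

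The share q of patients with a presenting event is not in the protocol. Assume that it is the same in both phases, that all such events are counted, and that they are independent of later events. Each rate then becomes p′ = q + (1 − q)·p.

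| q (assumed) | Before | After | Risk ratio | Power, corrected | Power, uncorrected | N per phase for 80%, corrected |
|---|---|---|---|---|---|---|
| 0 | 9.00% | 5.50% | 0.611 | 80.0% | 82.4% | 917 |
| 1% | 9.91% | 6.45% | 0.650 | 74.7% | 77.3% | 1038 |
| 2% | 10.82% | 7.39% | 0.683 | 69.6% | 72.4% | 1161 |
| 5% | 13.55% | 10.23% | 0.755 | 56.7% | 59.5% | 1546 |
| 10% | 18.10% | 14.95% | 0.826 | 41.8% | 44.3% | 2245 |

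**5. Sensitivity to the model**

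If presenting events instead add q to both rates and leave the 3.5-point difference intact, corrected power is 75.2%, 70.8%, 60.1% and 48.5% for q = 1%, 2%, 5% and 10%. The loss is smaller but has the same direction.

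**The case against.** The strongest defence is that section 8.1.1 can be read sensibly: medication start for patients who begin in hospital, hospitalization for those already on treatment. On that reading, an untreated patient admitted with a pulmonary embolism has the event before the window opens, and it is not counted. A reader might infer that every stated window counts the presenting event. The protocol does not support that, since the medication-start reading excludes it for new users. But the protocol does not state this allocation of starting points either, and section 8.3.1 does not carry it.

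A reader might also infer that events from years of earlier treatment enter the endpoint. They do not: Table 3 has no field for events before hospitalization. This limits the practical damage of the medication-start wording, but it also means that, for current users, that window cannot be filled from the planned data.

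It is also fair to say that an event which caused an admission did not, read literally, occur during it, and that Table 3 keeps the reason for admission apart from the outcomes. So it is an inference, not a stated instruction, that such patients meet the endpoint on the day they arrive. What stands is that events are read from a record containing the admission diagnosis, with no new-onset rule.

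An analysis plan could add onset rules, but two conflicting definitions of the primary endpoint would remain in the protocol.

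**Conclusion.** The concern holds as an inconsistency in the definition of the primary endpoint, joined to the absence of any rule on the presenting event. It should be corrected in the protocol.

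The effect on power is conditional. A reader might conclude that the stated 80% is lost; the protocol does not show that, because it gives no share of patients admitted with a bleed or thrombosis. Under the model in step 4 of the working, corrected power is about 70%, 57% or 42% at assumed shares of 2%, 5% or 10%. Dilution is the expected direction if such events are counted equally in both phases; its size is not known. Equal shares in the two phases are themselves an assumption, and if they differ the problem becomes bias as well as lost power.

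Two qualifications remain. The S-team's consultation role outside the hospital (section 5.1) could reach a few patients before admission, so it is too strong to say that it can never prevent a presenting event. And the planning rates in section 4.4 are annual and start from major bleeding, whereas the endpoint covers admission plus 3 months and includes non-major bleeding. The 80% is thus a reference point taken from the protocol's own rates, not a verified baseline.

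**What to change.** Use one window in the Summary, 8.1.1, 8.1.2 and 8.3.1:

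- **Start, current users:** index admission.
- **Start, patients who begin in hospital:** one pre-specified point, either admission or first antithrombotic dose, the same in both phases.
- **End:** 3 months after discharge.
- **Events:** only those with new onset after the start. State that an event which is the reason for admission, or is present at admission, is not an endpoint event, and use the recorded "Reason for hospitalization" to apply this.
- **CRF:** add the onset date of each endpoint event to Table 3.

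A single anchor at the later of admission and first in-hospital dose for everyone looks simpler but should be avoided. It would drop genuine in-hospital events in current users before their first inpatient dose, leave patients without an inpatient dose with no time zero, and let the S-team influence when the window opens.

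The cost is a wording change in four places and one CRF field. The downside is fewer counted events. On the protocol's own rates, excluding presenting events leaves 917 per phase and 80% power as planned.

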#### 8.1.2 Secondary study parameters/endpoints

- Proportion of patients with  $\geq 1$  bleeding (major bleeding and mild to moderate clinically relevant non-major bleeding) event from time to start with antithrombotic medication (or hospitalization) until 3 months after hospitalization.
- Proportion of patients with  $\geq 1$  thrombotic event from time to start with antithrombotic medication (or hospitalization) until 3 months after hospitalization.
- Severity of bleeding complication
- Length of hospital stay (LOS)
- Percentage of readmissions within 3 months after discharge
- Patient related outcomes (quality of life, adherence of patient to therapy and patient satisfaction with the quality of care of the antithrombotic therapy)
- Adherence to the hospital protocol
- Healthcare costs (labor costs versus costs for bleeding/thrombotic events (including use of antidotes))
- All-cause mortality
- Percent time in therapeutic range of vitamin K antagonists during hospitalization and 3 months after discharge.

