Studies on the effect of a multidisciplinary antithrombotic team are scarce. Antithrombotic services are described mainly as pharmacist-led antithrombotic services in US hospitals that are predominantly aimed at warfarin dosing. This differs from the Dutch situation, where Thrombosis Services with a medical leader are responsible. In only 4 of 25 respondents of a survey such an antithrombotic service was multidisciplinary. One article describes an expanded antithrombotic stewardship, including both NOAC treatment and facilitating care after hospital discharge. It concerned a US one center pharmacist-led stewardship and the study included only a small retrospective control group of 12 patients. The majority of results were described for 409 patients monitored after implementation of the program. Also, the transition after discharge included only 34 patients, with 30 of them on warfarin therapy. Interventions consisted of changes to a more appropriate antithrombotic according to guidelines and dosing corrections. The length of hospital stay was reduced by 1.5 days and cost savings were \$270320 in 1.5 years. Discharge patient education and knowledge of patients is described in a few studies, but again mostly on warfarin. Given the known effect of patient education on adherence, patient education will be much more important for the NOAC therapy in which monitoring cannot be used to verify adherence.

The (lack of) implementation of the LSKA, and the shifting responsibilities regarding NOACs need solutions aiming at safe use of antithrombotics. The intervention in the present study consists of the implementation of an S-team. An S-team can be made responsible for LSKA implementation, can act as an expert team that can be consulted both from in- and outside the hospital, can take care of adequate handovers of patients discharged from hospital, and can improve patient education. A properly informed patient will more likely use antithrombotics safely and adherently, resulting in less complications.

At present the effectiveness of a multidisciplinary antithrombotic team is unknown. Therefore, the main objective of this study is to determine the effect of a multidisciplinary antithrombotic team ('S-team') on the frequency of bleeding and thrombotic events in two Dutch hospitals.

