### 8.3.1 Pre-intervention phase

During a 9-month period usual care is provided to patients. This means that antithrombotic therapy, related patient instructions and handover after discharge are carried out by the physicians responsible for the patient. Patients that are or will be treated with antithrombotics in the Erasmus MC and in the Reinier de Graaf hospital will be included with the help of a clinical rule. The criteria on which the clinical rule screens are the use of antithrombotic drugs which are listed in table 1 and the use of antidotes which are listed in table 2.

Table 1: Antithrombotic agents

| Group of antithrombotic agents (ATC code) | Antithrombotic agents (ATC code) |
|-------------------------------------------|----------------------------------|
| Vitamin K antagonists (B01AA)             | Phenprocoumon (B01AA04)          |
|                                           | Acenoucoumarol (B01AA07)         |
| Heparin group (B01AB)                     | Heparin (B01AB01)                |
|                                           | Antithrombin III (B01AB02)       |
|                                           | Dalteparin (B01AB04)             |
|                                           | Enoxaparin (B01AB05)             |
|                                           | Nadroparin (B01AB06)             |
|                                           | Danaparoid (B01AB09)             |
|                                           | Tinzaparin (B01AB10)             |
| Direct thrombin inhibitors (B01AE)        | Bivaluridin (B01AE06)            |
|                                           | Dabigatran etexilate (B01AE07)   |
| Direct factor Xa inhibitors (B01AF)       | Rivaroxaban (B01AF01)            |
|                                           | Apixaban (B01AF02)               |
| Other antithrombotic agents (B01AX)       | Fondaparinux (B01AX05)           |

Table 2: Antidotes

| Group of antihemorrhagics (ATC code) | Antihemorrhagics (ATC code)                                   |
|--------------------------------------|---------------------------------------------------------------|
| Amino acids (B02AA)                  | Tranexamic acid (B02AA02)                                     |
| Vitamin K (B02BA)                    | Phytomenadione (B02BA01)                                      |
| Fibrinogen (B02BB)                   | Fibrinogen, human (B02BB01)                                   |

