| Blood coagulation factors (B02BD)    | Coagulation factor IX, II, VII and X in combination (B02BD01) |
|                                      | Eptacog alfa (activated) (B02BD08)                            |
| Antidotes (V03AB)                    | Protamine (V03AB14)                                           |

New antithrombotic agents and antihemorrhagics entering the market, are also included in the study when they are introduced in the hospital.

During the hospitalization for each included patient data are collected in a case report form (CRF). Detailed information on the data can be found in table 3.

Table 3: Content of case report (CRF)

| Part           | Data content                                                                                                                                                                                                                                          |
|----------------|-------------------------------------------------------------------------------------------------------------------------------------------------------------------------------------------------------------------------------------------------------|
| Patient data   | Patient ID                                                                                                                                                                                                                                            |
|                | Date of birth*                                                                                                                                                                                                                                        |
|                | Gender*                                                                                                                                                                                                                                               |
|                | Weight on the first day of hospitalization*                                                                                                                                                                                                           |

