|                 | All-cause mortality**                                                                                                                                                                                                                                                                                                                                                                                                                                                                                                                                                                                                                      |
| Clinical data   | 
Laboratory values and the date of determination**
 
 
- International Normalized Ratio (INR)
 
- Activated Partial Thromboplastin Time (APTT)
 
- Prothrombin time (PT)
 
- Diluted Thrombin Time (dTT)
 
- Hemoglobin (Hb)
 
- Antifactor Xa (Anti-Xa)
 
- Creatinine
 
- Hematocrit (HT)
 
- Erythrocytes
 
- Thrombocytes
 
- Estimated Glomerular Filtration Rate (eGFR)
 
- Weight
 
 
(Available clinical data is collected from 3 months before inclusion till 3 months after hospitalization)
 |
| Medication data | Medication use during hospitalization (coded with ATC-code  )*                                                                                                                                                                                                                                                                                                                                                                                                                                                                                                                                                                |

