#### ***Percent time in therapeutic range of vitamin K antagonists***

INR data are collected during and 3 months after hospitalization. Therapeutic INR range (TTR) is a way of summarizing INR control over time.

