### **8.3.3 Post-intervention phase**

During a 9-month period the S-team is active. From the clinical rule patients with antithrombotics will be identified and presented to the S-team. The main tasks of the S-team will be:

- Drafting of local guidelines
- Monitoring of the medication by the hospital pharmacist/clinical pharmacologist focused on patients that are treated with antithrombotics
- Patient instructions
- Proper handover to either the Thrombosis Service or the general practitioner, and to the community pharmacist, at the moment of hospital discharge
- Educating physicians, nurses and hospital pharmacists
- Offering consultation for professionals in- and outside the hospital

During the post-intervention phase the same data are collected as during the pre-intervention phase.

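### Mean time in therapeutic range is compared only among patients still on a vitamin K antagonist, so a phase difference in who stays on one can distort the comparison in either direction

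*Protocol*

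**What the plan says.** The TTR endpoint in section 8.1.2 of the protocol is "Percent time in therapeutic range of vitamin K antagonists during hospitalization and 3 months after discharge". The TTR paragraph in section 8.3.1 gives the source: "INR data are collected during and 3 months after hospitalization". Section 10.2 plans linear or logistic regression for secondary outcomes. Section 8.2 marks randomisation as not applicable.

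In the pre-intervention phase the treating physicians decide on therapy: "This means that antithrombotic therapy, related patient instructions and handover after discharge are carried out by the physicians responsible for the patient". In the post-intervention phase the S-team also drafts local guidelines, educates, consults and carries out "Monitoring of the medication by the hospital pharmacist/clinical pharmacologist focused on patients that are treated with antithrombotics" (section 8.3.3). Changing the drug is not named among its tasks.

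The introduction describes one expanded stewardship service that also covered non-VKA oral anticoagulants: "Interventions consisted of changes to a more appropriate antithrombotic according to guidelines and dosing corrections". Direct thrombin and factor Xa inhibitors are already in Table 1, and section 8.3.1 adds: "New antithrombotic agents and antihemorrhagics entering the market, are also included in the study when they are introduced in the hospital".

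Table 3 includes INR among the laboratory values and notes: "Available clinical data is collected from 3 months before inclusion till 3 months after hospitalization". It also collects medication use for three months before and after the stay.

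**The concern.** A patient contributes TTR only for time on a VKA. Whether a patient is on a VKA after admission is decided once the intervention can already act, through guidelines, medication monitoring and advice to prescribers. It can also drift with calendar time, because the two phases follow one another in a study that runs from 2015 to 2018. Each phase's mean TTR therefore depends on INR control and on which patients remain on, or are started on, a VKA.

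At stake is the reading of the TTR result. A higher mean could reflect fewer poorly controlled patients in the denominator, and an unchanged or lower mean could hide a real improvement. Without randomisation, nothing else in the design makes the two VKA groups comparable. The primary composite endpoint is not affected.

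**Working it through.** **Plan's own figure.** The protocol gives none for TTR: no mean, SD, switching rate or number of patients with evaluable TTR. Its 917 per phase is for the primary composite. It reproduces from 9% versus 5.5%, alpha 0.05 two-sided, power 0.80, with continuity correction, and has no bearing here.

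**Inputs, all assumed.** SD of patient-level TTR: 20 to 25 points. Extra proportion f of VKA patients leaving the TTR set in one phase compared with the other: 5%, 10% or 20%. No true change in anyone's INR control. Leavers contribute no TTR at all, which overstates the shift for anyone with INR time before a switch. VKA patients per phase for the standard error: 350. Section 4.4 expects over 700 VKA users admitted to one hospital in 9 months, but these are admissions, not enrolled patients with evaluable TTR.

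**Case A: leaving unrelated to control.** Shift = 0.

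**Case B: moderate selectivity.** The worse-controlled half leaves at 1.5f and the better half at 0.5f, a ratio of 3 to 1. Under a normal distribution the half means lie 0.798 × SD either side of the overall mean, so

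shift = 0.798 × SD × (1.5f − 0.5f) / (2 − 2f) = 0.798 × SD × f / [2(1 − f)].

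For SD 20 and f = 0.05: 0.798 × 20 × 0.05 / 1.9 = 0.42.

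**Case C: extreme.** Exactly the worst-controlled fraction f leaves: shift = SD × φ(z_f) / (1 − f), where φ is the standard normal density and z_f the f quantile.

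For SD 20 and f = 0.05: 20 × 0.103 / 0.95 = 2.17.

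**Standard error** = SD × √[1/350 + 1/(350(1 − f))].

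| SD | f | Case B shift | Case B shift / SE | Case C shift | Case C shift / SE |
|---|---|---|---|---|---|
| 20 | 5% | 0.42 | 0.27 | 2.17 | 1.42 |
| 20 | 10% | 0.89 | 0.57 | 3.90 | 2.51 |
| 20 | 20% | 1.99 | 1.24 | 7.00 | 4.36 |
| 25 | 5% | 0.52 | 0.27 | 2.71 | 1.42 |
| 25 | 10% | 1.11 | 0.57 | 4.87 | 2.51 |
| 25 | 20% | 2.49 | 1.24 | 8.75 | 4.36 |

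**Direction.** Case B is symmetric. If the better-controlled half leaves at three times the rate of the worse half, the shift is the same size with the opposite sign, −0.4 to −2.5 points.

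**The case against.** **A stronger reading.** A reader might infer that the S-team moves poorly controlled patients off VKAs in the post-intervention phase only, so that mean TTR must rise. The documents do not support this, for three reasons.

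- Physicians could switch patients under usual care, the newer agents are already listed, and further agents are included whenever the hospital introduces them. Only a difference in switching between phases matters.
- The drug changes described in the introduction come from another kind of service: "It concerned a US one center pharmacist-led stewardship and the study included only a small retrospective control group of 12 patients". The protocol itself says such services differ from the Dutch situation. It does not say that the changes were away from VKAs or concerned poorly controlled patients.
- A switched patient still contributes INR time before the switch.

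**A stronger number.** One might also put the shift at roughly 1.5 to 2 standard errors when 10% of VKA patients leave. Simulating TTR as normal with mean 60 and SD 25, clipped to 0 to 100, and deleting 10% of patients, all from the lowest third, raises the mean by 2.95 points. The standard error 25√(2/n) is 1.89 at n = 350 and 1.34 at n = 700, so the ratio is 1.6 to 2.2. The figure holds only if every leaver comes from the lowest third and is removed entirely. Nothing in the protocol supports either condition, and with 3 to 1 selectivity the same 10% gives 0.57 standard errors.

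**Missing detail.** The analysis set and covariates of a secondary endpoint are usually left to a statistical analysis plan, which is not at hand, and section 10.2 excludes no covariate. That objection stands against any complaint about a missing scoring rule. It does not remove the structural point: the endpoint as defined depends on treatment received after the intervention starts, in a non-randomised comparison.

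**Conclusion.** The point holds in limited form. If VKA stopping or switching differs between phases and is related to INR control, the difference in mean TTR is distorted, and its sign cannot be known in advance. The size cannot be derived from the protocol. On the assumed inputs it is 0 without selectivity, about 0.4 to 2.5 points (0.3 to 1.2 standard errors at an assumed 350 per phase) with moderate selectivity, and 2.2 to 8.8 points only when exactly the worst-controlled patients leave. A calendar shift to newer agents is plausible from the protocol's own rationale, but the protocol does not quantify it.

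TTR is the last of ten secondary objectives, so this is a limited matter. It deserves action because the data for a better comparison are already being collected.

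**What to change.** Add to section 10.2, for the TTR endpoint:

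1. For patients using a VKA before admission, adjust the regression for INR control in the 3 months before inclusion, where those INRs are available.
2. Analyse patients without prior VKA use as a separate stratum rather than dropping them.
3. Count TTR time up to the point at which the VKA is stopped.
4. Report, per phase, the number whose VKA was stopped or switched, with their prior INR control, so that a reader can see whether leaving was selective and whether it differed between phases.

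The cost is analysis wording and one table. INR values and medication records before and after the stay are already in Table 3. The downside is that pre-inclusion INRs will be missing for some patients, because only available values are collected. The number missing should be shown.

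Some selection remains. Adjustment handles selection on earlier control, but not on INRs during the study, and it cannot help patients newly started on a VKA. For those, the counts in item 4 and the separate stratum are the safeguard.
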